**PASHOS Project: Advanced Platform for Obstructive Sleep Apnea (OSA) Assessment:**  
**A Multi-Centre Study for the Validation of a OSA Screening Model in Primary Care**

**SUMMARY OF THE PROJECT PROPOSAL:**

**Study General Objective:**

The purpose of this study is to develop and validate a work-model for Primary Care for identifying patients with Obstructive Sleep Apnea Syndrome (OSA), based on clinical variables and an ambulatory monitoring study.

**Study Specific Objectives:**

- .- To establish the validity of an Ambulatory Monitoring Study (AMS) for identifying patients with OSA, compare it with Sleep Unit studies, Polygraphy (RP) and Polysomnography (PSG), and create a screening model for the detection of OSA in Primary Care.
- .- To analyze the validity of the therapeutic decisions (CPAP) made by Primary Caregivers, in comparison with the therapeutic decisions made by Sleep Unit specialists.
- .- To analyze the cost-effectiveness of AMS.

**Methods:**

Prospective multicenter study. Patients aged between 18-75 years visited at Primary Care consultations will be included according to a randomization schedule to reach the sample size (198). The study involves 4 Sleep Lab Units and 6 Primary Care Centers in Barcelona. Two models of evaluation will be used: one in the Primary Care center and the other in the Sleep Lab Units. **Outcomes:** anthropometric data, cardiovascular history and risk factors, self-assessed questionnaire of sleep disorders, ambulatory monitoring study data and polygraphic/polysomnographic data. **Statistical analysis:** Calculation of the area under the curve (AUC) of the ROC curve (Receiver Operating Characteristics). The best clinical prediction model will be detected by using logistic regression. Variables with clinical significance in the bivariate analysis and variables considered clinically relevant will be included. The resulting model will be validated with the goodness-of-fit test (Hosmer and Lemeshow test). **Cost analysis:** Methodology according to Pietzoch JB et al. Sleep 2011; 34: 695-709.

## **DETAILED DESCRIPTION OF THE PLANNED PROGRAM INCLUDING MILESTONE AND TIME PLANNING**

### **Background**

Obstructive Sleep Apnea (OSA) is a highly prevalent disorder in the general population (1). It is associated with an impaired quality of life (2) and an increased work and traffic accident risk (3). It is also associated with high blood pressure (4), diabetes mellitus (5), cardiovascular and cerebrovascular diseases and increased mortality (6).

OSA is characterized by repeated episodes of airflow cessation that cause cyclic falls of arterial oxygen saturation and arousals. These consequences decrease sleep quality and result in non-refreshing sleep. Daytime sleepiness is one of the main symptoms of patients with OSA and produces impaired cognitive functions, lack of concentration, loss of memory, coordination difficulties and impaired quality of life. Repeated episodes of hypoxia-reoxygenation and an increase of sympathetic activity can stimulate different pathogenic pathways such as oxidative stress, endothelial dysfunction, hypercoagulability and insulin resistance causing atherogenesis. These disturbances create a greater risk of cardiovascular and metabolic diseases (7).

The severity of this syndrome is defined by the apnea-hypopnea index (AHI). The AHI is obtained by dividing the apnea (total occlusion) and hypopnea (partial occlusion) number by the hours of sleep. An AHI > 15 is associated with increased cardiovascular risk, with or without symptoms, and this risk is greater at AHI > 30 (8).

It is estimated that between 3-6% of the Spanish population present this syndrome. This prevalence increases to 24-25% in cases of a high AHI without symptoms (1). In some risk-populations the presence of OSA is very high. About 30% of patients with arterial hypertension have OSA (9). This figure increases to 80% in patients with hypertension refractory to medical therapy (10).

Our research group has recently shown a prevalence of 72% in morbidly obese candidates for bariatric surgery (11).

Patients with OSA double their use of sanitary resources during the ten years before diagnosis, including hospitalizations. A high percentage of the cost of this syndrome arises from other social consequences such as poor work performance and traffic accidents (12). In the U.S.A. the estimated total cost of OSA is greater than the outlay for other chronic diseases such as asthma and COPD and equals the outlay for diabetes mellitus (13).

Basic treatment consists of applying continuous positive airway pressure (CPAP) during sleep. CPAP is an effective treatment that corrects obstructive respiratory disturbances and improves symptoms and quality of life.

In different randomized, placebo controlled trials, CPAP has demonstrated a significant reduction in hypertension and an improvement of insulin resistance (14). In patients with severe OSA, CPAP treatment decreases mortality due to cardiovascular disease (6).

The guidelines establish the use of CPAP depending on the severity of the disorder, its impact on the quality of life and its possible association with cardiovascular, cerebrovascular or respiratory diseases. In general, CPAP is indicated in patients with severe OSA and in those with moderate OSA with relevant symptoms or comorbidity (8,15).

Although the number of Sleep Units has increased considerably over the last few years, available resources are still insufficient for all the demand for care generated by OSA (16). In our public-health area (Barcelona Eixample Dreta), the delay time estimated for a screening study is 6 months. If a study suggests the presence of a respiratory sleep disorder, the delay time for a diagnostic study increases by an additional 6 months.

The diagnosis of OSA is based on a sleep study that detects different disturbances (apneas, hypopneas and episodes of airflow limitation) and their immediate consequences (arterial desaturation, arousals, heart rhythm disorders, etc). Conventional polysomnography (PSG), monitored by a technician in the sleep laboratory, is the gold standard diagnostic test for suspected OSA. PSG is an expensive, laborious and technically complex technique and is not available at all centers. To address these difficulties, portable devices that record only respiratory variables have been developed, such as respiratory polygraphy (RP). RP is a diagnosis validated method in a high percentage of patients (8,13). It is easier to interpret than PSG but also requires training and experience in signals analysis.

Recently, even simpler ambulatory monitoring devices have appeared on the market. They are extremely user-friendly, in terms of both use and analysis. These tools can play an important role in disease detection outside hospital Sleep Units, especially for at-risk populations and patients with serious illness.

Although these devices are designed to be used by non-expert personnel, the validation studies existing until now have been conducted in specialized Sleep Units (17). These systems are therefore not being used at the healthcare level for which they were designed initially.

Currently, the Primary Care physician (PCP) usually refers all patients with suspected OSA to the specialist, without considering clinical probability (high or low) or comorbidity. The prevalence of symptoms related to OSA in patients visited for any reason by PCPs is far higher than for the general population (same age and gender) (18). That is because the population attended at Primary Care centers has specific characteristics: being more obese and with more comorbidities. Additionally, several series have shown that PCPs have a surprisingly low level of suspicion of this disease, even in clearly at-risk populations (19). For example, in the city of Barcelona, the diagnosis of OSA is listed in only 1.49% of the computerized medical records. Specifically, in the “Dreta de l'Eixample”, one of the areas where this project will be carried out, the diagnosis of OSA appears in only 1.38% of the records.

These results can be explained by lack of information about this relatively recent disease, the poor relationship between Sleep Units and Primary Care, and the difficulty in identifying symptoms suggestive of OSA.

The immediate future of the management of OSA requires coordination between all levels of healthcare: Sleep Units at hospitals, less complex units and Primary Care centers. It also requires the inclusion of simple screening tools, outside hospitals, for detecting patients requiring priority attention. In this regard, outside our country, the results of some experiences with very promising results have recently been published. Chai-Ch L Coetzer et al. (20) validated a screening model in 150 patients in Primary Care centers. This model included clinical variables and a home overnight oximetry study. The diagnostic profitability of the model showed a sensitivity of 0.88 (95% CI from 0.60 to 0.98) and a specificity of 0.82 (95% CI 0.70-0.90). It must be taken into account that these were consecutive patients visited in Primary Care centers, without a previous clinical suspicion of OSA. The same research group analysed the clinical efficacy and costs of an integral model for patients with OSA at Primary Care level, including therapeutic management (21). The study showed comparable results in terms of clinical and cost outcomes at Primary Care level versus specialized care. Until now, similar projects have not been carried out in our country.

## **Rationale**

The purpose of this project is to assess the efficacy of a sequential screening model in Primary Care centers for detecting and classifying patients with OSA according to severity. The clinical model used will, like recent studies published in the literature, be based on a set of clinical variables and the data obtained by a simplified monitoring device.

To achieve this, we have at our disposal three Sleep Units, attending an urban population of more than one million inhabitants and six Primary Care groups with different administrative and operational structures.

If the results are as expected, this screening model will prove to be a simple tool for screening for OSA at Primary Care level, thereby making it possible to avoid the referral of a large number of patients to Sleep Units. After a first analysis at Primary Care level, PCPs would be able to rule out OSA and, moreover, prioritize patients with severe disease.

Finally, we believe that the availability of this screening-model will have a positive effect on the impact of this disease and its process costs.

## **Hypothesis**

It is possible to identify patients with OSA at Primary Care level with great diagnostic reliability by using a screening model that includes clinical variables and data provided by an ambulatory monitoring device.

The cost-effectiveness of this strategy, which includes the management of OSA at Primary Care level, is equal to or higher than the complete management carried out in the Sleep Unit.

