### Specific objectives:

- To establish the validity of an ambulatory monitoring device for identifying patients with OSA and to compare it with the RP / PSG performed at the Sleep Unit.
- To create a screening model for the detection of OSA.
- To analyze the validity of the treatment decision (CPAP vs. no CPAP) made by the PCPs, by using the ambulatory monitoring study, in relation to the decision made by the specialist Sleep Unit.
- To make an analysis of costs, including the cost-effectiveness of an outpatient strategy vs. a strategy including assessment at the Sleep Unit.

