#### 2.- Design and Validation Time:

All patients eligible for inclusion in the study will perform the two models of validation (in the Primary Care center or in the Sleep Unit), as shown below (Stages 1 and 2):

[figure not shown]

Ambulatory Monitoring Study (AMS):

The study will be performed in the patient's home with a Screen & GO device (BITMED, SibelGroup, Spain). The Primary Care nurse will record the anthropometric variables on the day before the test, will train the patient in the use of the device and will program it according to the usual sleep rhythm of the patient. To ensure the correct management of the equipment, a sheet with some instructions will be given to the patient.

The device will be returned to the Primary Care center the following morning. A brief questionnaire about the quality of sleep on the night of the study will be collected, estimating the start and end of the test. The nurse will be responsible for analyzing the quality of the study and will remove periods of poor signal but will not analyze the respiratory events manually: the recording time will be defined as the time passed from 15 minutes after sleep onset (according to previous questionnaire) to 10 minutes before completion. The minimum valid record-time will be 5 hours.

The analysis of the study will be done automatically by the device software. The following variables will be collected: mean SO2, ID4%, ID3%; CT90% and AHI.

The study could be repeated (only once) if a high percentage of poor signal acquisition is detected or if the patient reports poor quality of sleep during the night of the study.

To complete the assessment, a standard sleep study by RP / PSG will be performed, allowing for the final validation of the process.

The final treatment decision will always be made by the physician involved in the project, either in the Primary Care centre or in the Sleep Unit.

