RP / conventional PSG: in every case, an overnight sleep study will be done in the Sleep Unit. Conventional PSG must include at least 6 channels: electroencephalography (EEG), electrooculography (EOG), mental electromyography (EMG), hemoglobin oxygen saturation detected by oximetry, oro-nasal airflow by thermistor and nasal-cannula, thoraco-abdominal movements by inductance plethysmography, electrocardiography (ECG), anterior-tibial electromyography and body position. RP will include every channel except EEG, EOG, EMG and ECG. The staging of sleep and respiratory events will be analyzed by the technician of the Sleep Unit, who will be blind to the results of the study at Primary Care level. The sleep study will be classified according to published guidelines (AASM 2007, SEPAR Manual procedures). The minimum recording time should be 6 hours and the minimum total sleep time, 3 hours.

The following data will be collected: Apnea-hypopnea index (AHI), obstructive apnea index, hypopnea index, central apnea index, mixed apnea index, sleep efficiency (total sleep

time/record time), percentage of time in phases NREM1, NREM2, NREM3 and REM, initial saturation, mean saturation (SO2), minimum saturation and cumulative time percentage with saturation lower than 90% (CT90%).

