#### Data management and analysis

The main objective of this study is to obtain a sufficiently accurate calculation of the area under the curve (AUC) of the Receiver Operating Characteristics (ROC) curve. The expected sensitivity value is high, close to 90%. With this number of cases the accuracy of the AUC will not be less than 10%. In all cases, the interval confidence of calculated rates is assumed to be 95%.

A descriptive analysis will be performed using means, medians, confidence intervals, interquartile ranges for quantitative variables and table of frequencies for qualitative variables. In qualitative variables, the Chi-square test or Fisher exact test will be used for bivariate analysis. In the case of quantitative variables, the T-test or Mann-Whitney U test will be performed according to normal distribution.

Finally, logistic regression will be used to find the best clinical prediction model. Variables showing clinical significance in the bivariate analysis and those considered clinically relevant will be included. A goodness-of-fit test (Hosmer Lemeshow test) will be performed to validate the resulting model. The AUC of the ROC will be used to calibrate the model.

In all cases, the significance level will be, as usual, 5% ( $\alpha = 0.05$ ), bilateral approach.

We will use IBM-SPSS (V. 21.0) software to perform the analysis.

In the analysis of costs we will consider the direct costs of all the tests (ambulatory monitoring study, polygraphy or polysomnography), staffing costs, the amortization of the devices, the transfer of the patients and the number of visits. We will also take into account the false-positive and negative diagnosis (*Pietzoch JB et al. An integrated Health-Economic Analysis of Diagnostic and Therapeutic strategies in the treatment of moderate to severe obstructive sleep apnea. Sleep 2011;34: 695-709*).

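### The second hypothesis claims cost-effectiveness of managing OSA in Primary Care, which goes beyond the cost objective and beyond what the study's own data can show

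*Protocol*

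**What the plan says.** The Hypothesis section of the protocol states: "The cost-effectiveness of this strategy, which includes the management of OSA at Primary Care level, is equal to or higher than the complete management"; its comparator is the Sleep Unit. The Specific objectives section sets a narrower economic aim, "the cost-effectiveness of an outpatient strategy vs. a strategy including assessment at the Sleep Unit". It treats therapy only as a decision to be checked against the specialist's: "To analyze the validity of the treatment decision (CPAP vs. no CPAP) made by the PCPs".

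Under Design and Validation Time, "All patients eligible for inclusion in the study will perform the two models of validation", and for RP/PSG, "in every case, an overnight sleep study will be done in the Sleep Unit". On treatment, "The final treatment decision will always be made by the physician involved in the project", at either level of care.

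The Data management and analysis section begins its cost paragraph with "In the analysis of costs we will consider the direct costs of all the tests (ambulatory monitoring study, polygraphy or polysomnography"). It adds staffing, device amortisation, patient transfers, number of visits, and false-positive and false-negative diagnoses. It refers to a published integrated health-economic analysis of diagnostic and therapeutic strategies, which the project summary also names as the cost method.

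**The concern.** The hypothesis and the objective ask different questions. The objective asks whether an outpatient route to diagnosis is worth its cost compared with a route through the Sleep Unit. The hypothesis asks whether looking after patients in Primary Care is at least as cost-effective as looking after them entirely in the Sleep Unit. The second question needs a measure of what management achieves at each level, and the protocol lists none.

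If both texts stand, a favourable result on diagnostic costs and classification errors could be reported as confirming the hypothesis. It would then be read as evidence for moving management, and not only screening, to Primary Care.

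**Working it through.** No single figure decides this point, so the main check sets the sections side by side.

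**What a management comparison needs, and what the protocol provides**

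| Needed | Provided | Section |
|---|---|---|
| Management at one level contrasted with management at the other | Both evaluations in every patient; one final treatment decision, taken at either level | Design and Validation Time |
| An effect of management (quality of life or utility, CPAP use, symptoms after treatment) | Sleep-study AHI as primary outcome; anthropometry, history, Berlin, Epworth, spirometry, RP/PSG and AMS variables; no repeat after treatment described | Outcome Measures |
| Observation after the decision | No follow-up visit or duration in the readable text; the task list goes from recruitment to the end of the Sleep Unit study, then analysis | Design and Validation Time; Time Planning |
| Cost of treatment and follow-up | Tests, staff, devices, transfers, visits, diagnostic errors; treatment not named | Data management and analysis |

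The Background section itself separates the two questions. It cites one study that validated a screening model and another, by the same group, that examined efficacy and costs including therapeutic management. This protocol has a design of the first kind and a hypothesis of the second.

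**What the paired data can support**

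The only stated size, 198, is built on sensitivity. The stated inputs (prevalence 25%, sensitivity 90%, error 5%, power 90%, losses 15%) do not fix it, because no null value is given. With an assumed null sensitivity of 0.70, two-sided, the one-sample formula gives 42 patients with OSA; 42 / 0.25 = 168; 168 / 0.85 = 197.6, so 198. No size or margin is stated for cost-effectiveness.

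- Evaluable patients: 198 × 0.85 = 168.
- Sensitivity of 0.90 with 42 OSA patients: 95% half-width 1.96 × √(0.90 × 0.10 / 42) = 0.091.
- Agreement of CPAP decisions in 168 patients, assuming agreement of 0.90 to 0.80: 1.96 × √(0.90 × 0.10 / 168) = 0.045, to 1.96 × √(0.80 × 0.20 / 168) = 0.060.

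Diagnostic correctness and agreement of decisions can thus be estimated to within a few percentage points. The effect of management at either level cannot be estimated from these data.

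**The sampling fraction**

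The Sample size section studies all patients with high Berlin probability and one in three with low probability, and asks for at least 396 questionnaires to reach 198. If h is the high-probability share, h + (1 − h)/3 = 198/396 = 0.5, so h = 0.25. That means 99 high and 297 low, of whom 99 are studied. Half of the studied sample is then high-probability, against a quarter of those screened. An unweighted cost per patient would not describe Primary Care. A weight of 3 restores the mix: 99 + 3 × 99 = 396.

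Weighting costs some precision. The approximate effective share is 396² / [198 × (99 × 1² + 99 × 3²)] = 156,816 / (198 × 990) = 0.80, or about 134 of 168 patients. The half-widths for agreement become 1.96 × √(0.09 / 134) = 0.051 to 1.96 × √(0.16 / 134) = 0.068.

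**The case against.** The strongest reply is that the protocol does plan an economic analysis by a cited method whose title covers therapeutic strategies. Such a model could carry false positives and false negatives through to health effects using outside inputs, and its structure, horizon and sources may properly sit in an analysis plan that is not shown. This stands against any statement that the hypothesis cannot be addressed at all. It does not remove the mismatch, because an analysis plan cannot supply outcomes that the protocol does not collect, and a modelled effect is not a finding of this study.

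Three stronger readings are tempting, and the documents do not support them.

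- A reader might infer that putting every patient through both evaluations is itself a flaw. It is not. Pairing suits the comparison in the Specific objectives, and the fix below relies on it.
- A reader might infer that nobody is followed. That would be an inference from silence: the Sample size section allows for losses to follow-up, and the figure of the two stages is not shown. What can be said is that no follow-up after the treatment decision is described in the readable text.
- A reader might infer that, because RP/PSG is done in everyone, the outpatient strategy's costs will be overstated by some calculable factor. The cost paragraph nowhere says that observed RP/PSG use would be charged to that strategy. Counting the false negatives of AMS makes little sense if it were. Any such factor would also need a referral rule that the readable text does not give, and an OSA prevalence in a Berlin-enriched sample that is not the 25% assumed for Primary Care attenders.

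**Conclusion.** The point holds as a mismatch of scope. The Hypothesis section goes further than the Specific objectives, the Outcome Measures and the listed costs. From its own data the study can report cost per correctly classified patient and cost per CPAP decision that agrees with the Sleep Unit's. It cannot show that management in Primary Care equals or exceeds complete Sleep Unit management in cost-effectiveness.

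The consequence is an over-broad conclusion on a secondary aim, not a bias in the diagnostic results, and no numerical size is attached to it. The conclusion assumes that the missing figure does not define separate management pathways or outcomes after treatment. The 99/99 split assumes that the 396 questionnaires were derived from the one-in-three rule. It is worth correcting because the remedy is cheap and the claim bears on where patients would be managed.

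**What to change.** 1. In Hypothesis, restate the second hypothesis in line with the Specific objectives: cost-effectiveness of the outpatient diagnostic strategy and treatment decision, compared with Sleep Unit assessment. Remove the reference to management at either level.
2. Name two effect measures: cost per correctly classified patient, and cost per CPAP decision concordant with the Sleep Unit's decision.
3. In Data management and analysis, state that each strategy is costed by applying its own decision path to the same paired patients, and write that path down if the figure does not already give it. State that RP/PSG done only because the protocol requires it is not charged to the outpatient strategy.
4. Weight patients with low Berlin probability by 3, so that costs and effects refer to the screened population, and use standard errors that allow for the weights.
5. If effects of management are presented, label them as modelled from external inputs, with sources, and not as a result of this study.

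This costs protocol wording and a short decision-path calculation on data already planned. It needs no added patients, visits or tests. The downsides are a narrower economic claim and, from the weighting, intervals for overall agreement wider by roughly half a point to one point.
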